### Methods

#### Sampling and participants

The patients are recruited from obesity centres across Germany. Currently, the participants will be recruited from seven obesity centres and it is possible that more obesity centres will participate. Of the seven obesity centres, four offer an mHealth intervention and three do not. The inclusion criteria are that patients are at least 18 years old, have a basic knowledge of the German language, and a BMI ≥ 30. During their first stay at the obesity centre, patients will be asked to participate in the study. Due to the nature of the study, neither participants nor staff can be blinded to allocation. Thus, patients attending an obesity centre that offers an mHealth intervention will be asked whether they want to take part in the mHealth intervention. The patients who agree to take part in such an intervention will be assigned to the intervention group, while those who do not want to take part in such an intervention will be assigned to the control group. Moreover, patients attending a obesity centre that does not offer mHealth interventions will be assigned to the control group. The patients will receive no financial compensation for their participation in the study.

Given the insufficient evidence for the effectiveness of mHealth obesity interventions [28], a small effect size was considered in the power analysis. Conservatively estimating the effect size by *η*^2^ = 0.01, *α* = 0.05, 1-*β* = 0.80, with two groups, a correlation on among repeated measures of *r* = .30 and a design with three repeated measurement occasions, using an ANOVA with repeated measurements (within-between interaction), the calculated total sample size is 225 participants, nearly equally distributed over two groups. Since we expect a dropout rate of about 50% [29], the plan is to recruit 450 patients.

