#### mHealth obesity intervention

The obesity intervention consists of three stays at an obesity centre with about six months between the stays. The first stay lasts three weeks and the two following stays last one week each. The focus for the time at the obesity centres lies on nutritional therapy and exercise therapy, delivered in both individual and group sessions. The stays at the obesity centres are organized by groups. Each new group consists of a maximum of twelve participants. It is intended that a group also stays together for the second and third stay at the obesity centre. However, depending on the patients’ availability, this is not always possible. Moreover, one criterion for another stay is that patients have not gained weight compared to their last stay.

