##### Quantitative data collection methods

The data collection will start in July 2021 and the recruitment of patients for the baseline measurement is planned to finish in May 2022. The data collection will include three measurements (see Fig. 1). For all patients, the baseline measurement will take place during the first stay at the obesity centre. The follow-up measurements are aligned with the patients’ stays in the intervention group. For patients from obesity centres who offer an mHealth intervention, the first follow-up measurement will take place during the second stay at an obesity centre and the second follow-up measurement during the third stay. Patients recruited from obesity centres that do not offer an mHealth intervention will have the first follow-up measurement after six and the second follow-up measurement after twelve months, with the questionnaires directly sent to them. Questionnaires will also be sent directly to patients who are in obesity centres that offer an mHealth intervention (and thus potentially include further stays at the obesity centre), but do not attend them (e.g., due to weight gain, another stay was not approved by the insurance provider). Depending on the patients’ preference, the questionnaires will be sent either by e-mail or by post and a reminder will be sent if the patients do not return the questionnaires within two weeks.

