#### Body weight

The body weight will be provided by the obesity centres if the patients agree that this information can be forwarded. In case the patients are not at the obesity centre during the measurement, the patients will be asked to report their weight themselves. The patients will be asked to wear light clothing and no shoes during the measurement and to report their weight to the nearest 0.1 kg.

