### Data analysis

#### Data analysis of quantitative data

All data related to personal information will be pseudo-anonymized. Data will be entered by a research assistant and checked independently for their accuracy by another research assistant. Multiple imputation or the full-information maximum likelihood approach will be employed to treat missing data [47]. We will conduct two analyses: (a) with all patients who agreed to participate in the intervention and (b) with only those patients who completed the intervention (i.e., they had three stays at an obesity centre). A multivariate analysis of variance with repeated measurements (2 groups x 3 time points) will be used to analyze the effects of the intervention on the dependent variables (i.e., body weight, physical activity, eating style & behaviour, health-related quality of life). For the analysis of the structure of determinants of physical activity (i.e., motivation, intention, self-efficacy, enjoyment, habit) and its interdependencies, structural equation modeling procedures will be applied. In particular, the development of the dependent variables will be analyzed using latent growth curve models [48]. Moreover, mediation analyses will be conducted to test whether the determinants of physical activity mediate the effects of the intervention on physical activity behaviour. The effects of age, gender, frequency of participation in the mHealth application (supplied by the provider), and the physical activity level outside of the intervention will be controlled.

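### At mHealth centres the weight-gain rule decides whether follow-up weight is measured on site or requested by questionnaire; if gainers respond less often, multiple imputation or FIML would overstate weight loss there

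*Protocol article*

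**What the plan says.** All references are to the protocol article.

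- **Missing data** (Data analysis of quantitative data): "Multiple imputation or the full-information maximum likelihood approach will be employed to treat missing data". The text does not link this to the rule on further stays. The covariates it lists are age, gender, app use and outside physical activity; the reason for a missed stay is not among them.
- **Rule on further stays** (mHealth obesity intervention): "one criterion for another stay is that patients have not gained weight compared to their last stay".
- **Follow-up at centres offering the app** (Quantitative data collection methods): "the first follow-up measurement will take place during the second stay at an obesity centre and the second follow-up measurement during the third stay". This is worded for patients of those centres, so it covers app users and also patients who decline the app and become controls.
- **Fallback** (same section): questionnaires go to patients at these centres who could have further stays "but do not attend them (e.g., due to weight gain, another stay was not approved by the insurance provider"), and "a reminder will be sent if the patients do not return the questionnaires within two weeks".
- **Weight away from the centre** (Body weight): "In case the patients are not at the obesity centre during the measurement, the patients will be asked to report their weight themselves".
- **Control-only centres** (Quantitative data collection methods): questionnaires are sent at six and twelve months. Follow-up is not tied to a stay, although two of these three centres offer further stays (Control group).
- **Expected loss** (Sampling and participants): "Since we expect a dropout rate of about 50" per cent.

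**The concern.** At mHealth centres the outcome itself decides the route by which it is collected. A patient who has not gained can be weighed at the stay. A patient who has gained must answer a form after being refused one. Equal completeness by these two routes is a strong assumption when half the sample is expected to be lost.

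If gainers respond less often, the earlier weights do not reveal a gain that happened in the missing interval. A missing-at-random model then fills the gap largely from patients who held or lost weight, and mean loss at these centres is overstated. This reaches the analysis of all patients who agreed to take part, not only the analysis of patients with three stays. Part of the control group is followed by a different route, so the error need not cancel between groups.

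**Working it through.** **The plan's own figure.** With f² = 0.01/0.99 = 0.0101, r = 0.30, three occasions and N = 225, the noncentrality is λ = 0.0101 × 225 × 3/(1 - 0.30) = 9.74 on 2 and 446 degrees of freedom. Power is 0.802, and 225 is the smallest N that reaches 0.80. Then 225/(1 - 0.50) = 450. Both figures reproduce. The plan thus expects about 225 of 450 patients to be complete, roughly 112 per group.

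**Inputs for the illustration.** The article gives no means, SDs or return rates for weight, so these are assumptions: 6-month change normal with mean -4 kg and SD 7 kg in both groups (no true effect), baseline weight uninformative about change, 50% observed in each group. The missing-at-random estimate is then the mean change among those observed.

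1. Share who gain: 1 - Φ(4/7) = 0.284.
2. Mean change in gainers: -4 + 7 × φ(4/7)/0.284 = +4.36 kg. In non-gainers: -4 - 7 × φ(4/7)/0.716 = -7.31 kg. The gap is 11.67 kg.
3. If 30% of gainers are observed, non-gainers must be observed at (0.50 - 0.284 × 0.30)/0.716 = 0.58.
4. Gainers among the observed: 0.284 × 0.30/0.50 = 0.170.
5. Bias within that group: (0.170 - 0.284) × 11.67 = -1.3 kg.

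**Carried over to the group difference** (app minus control; negative favours the app). Rejection rates are simulated with 225 per group at baseline and nominal 5%.

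| Response pattern | Bias | Type I error |
|---|---|---|
| App gainers 30%; all controls missing at random | -1.3 kg | about 31-32% |
| Same; 25% of controls are decliners on the same schedule | -1.0 kg | about 19-20% |
| Same; 50% decliners | -0.7 kg | about 11-12% |
| Same; 75% decliners | -0.3 kg | about 6-7% |
| Gainers 30% in app group, 40% in control group | -0.7 kg | about 11% |
| Gainers 30% in both groups | 0.0 kg | 5% |
| Gainers 40% in app group, 35% in control group | +0.3 kg | about 7% |

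The decliner rows follow from step 5: with half the controls affected, the control mean carries half the bias and the difference is -1.3 × (1 - 0.5) = -0.7 kg.

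**Check over 12 months within one affected group.** This used normal-theory maximum likelihood on weights at 0, 6 and 12 months. Assumptions: baseline SD 22 kg, mean change -5 kg at 6 and -6 kg at 12 months, SD of change per interval 5 kg or 8 kg. The bias in 12-month change is:

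| Response, non-gainers / gainers | SD 5 kg | SD 8 kg |
|---|---|---|
| 50% / 50% | 0.0 kg | 0.0 kg |
| 60% / 40% | -0.9 kg | -1.5 kg |
| 70% / 30% | -1.8 kg | -3.3 kg |

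The error appears only when response differs between gainers and non-gainers.

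**The case against.** A reader might infer that the stay rule by itself makes weight missing not at random, and that the weight comparison is therefore biased towards the app. The article does not support either step.

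- **Weight is still sought.** Patients refused a stay, weight gain being a named example, get a questionnaire and a reminder and are asked for their weight. The rule changes the mode of collection. With equal response the bias is zero, and no return rates are given. This stands, and it makes the point conditional.
- **The direction is open.** Decliners at mHealth centres are controls on the same stay-based schedule, and mailed controls who gain may also fail to reply. If weight is under-reported, the control group, which relies more on self-report, would look better. Bias in favour of the app shrinks, vanishes or reverses accordingly. This stands too. Very large error rates come only from extreme inputs with every control treated as missing at random.
- **Weight is one of several dependent variables** in a multivariate analysis, so no single main weight comparison is named. That is correct. Weight loss is nevertheless called a primary goal in the Background and heads the list of outcomes in the study's primary purpose.
- **Auxiliary variables and sensitivity analyses commonly sit in the analysis plan**, which is not shown. Their absence here is no fault. The data item is different: if the reason for a missed stay is not recorded at the time, no later wording can recover it. The article does not show that it is recorded; sending the form requires only knowing that the stay was missed.

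The Discussion concedes selection bias and differences in centre procedures, but not follow-up that depends on the outcome.

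**Conclusion.** The point holds in conditional form. The route to a follow-up weight at mHealth centres depends on weight gain, about half of patients are expected to be lost, and the stated missing-data methods are not linked to the rule. If gainers return weights less often than attenders are weighed, weight loss at those centres is overstated, by about 1.3 kg in the central illustration at 6 months. The effect on the group difference ranges from about -1.3 kg, through about -0.7 kg with half the controls decliners, to 0 kg with matching response, and it can change sign. All of these figures rest on assumed means, SDs and response rates. They show what is possible and do not predict what this study will find. The matter merits a cheap improvement in data capture and analysis; it does not show that the planned analysis is biased.

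**What to change.** The change concerns recording and analysis only and leaves the rule on stays as it is.

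1. At each follow-up and in both groups, record whether a stay was attended and, if not, why: weight gain, other insurer refusal, patient choice, or unknown. Where a centre offers no further stay, record that as not applicable.
2. Record whether each weight was measured at the centre or self-reported.
3. Include the reason code and group as auxiliary variables in the multiple imputation or FIML model for body weight.
4. Report one delta-adjusted sensitivity analysis for body weight, shifting imputed values first in the app group only and then in both groups, and state the shift at which the conclusion changes.

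The cost is one extra coded field per follow-up plus a marker for how weight was obtained, one extra analysis, and somewhat wider intervals. The correction is only partial where the reason is unknown or where gainers who reply differ from those who do not.

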Obesity often results from an imbalance between too little energy expenditure and too much energy intake [14]. Therefore, to achieve weight loss as a primary goal, obesity interventions should help individuals be more physically active and eat healthier. Moreover, various studies indicate that obesity is negatively associated with indicators of health-related quality of life [15]. Individuals with obesity often report that because of their weight they experience physical complaints, have problems during their daily activities, or have difficulties to move in public [16]. In the same vein, individuals with obesity report often experiencing negative affective states, such as anger, fear or shame, in their daily life [17]. Because indicators of health-related quality of life are associated with the use of health services [18] as well as mortality [19], they are also important indicators of the success of an obesity intervention.

To increase the effectiveness of obesity interventions it is further important to understand the psychological processes that are associated with behaviour change [20]. In this study, we focus on the psychological processes related to physical activity. In this regard, a large number of studies shows that individuals who have a more autonomous motivation are more likely to be physically active [21]. In addition, dual-process theories that attempt to explain physical activity behaviour emphasize the role of both more explicit as well as more implicit psychological processes [22, 23]. On the one hand, individuals’ intention, self-efficacy, and enjoyment towards physical activity as more explicit processes have been consistently associated with physical activity [24–26]. On the other hand, habit is considered a more implicit process that has also been shown to be associated with physical activity [27].

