#### Control group

Patients who do not want to take part in the mHealth intervention will be assigned to the control group. In addition, there are three other obesity centres that do not offer an mHealth intervention from which patients will be recruited. In these centres, patients have their first stay in an obesity centre organized by groups with about twelve patients. During this stay, there are individual and group sessions with a focus on nutritional therapy and exercise therapy. When leaving the obesity centre, the patients will receive an exercise plan and dietary recommendations that should help them implement what they have learnt at the obesity centre. Equal to the intervention groups, all patients can receive additional therapies depending on their health status.

It is important to note that for logistical reasons, the involved obesity centres have differences regarding the type of intervention. While in two of the obesity centres the first stay of the patients lasts three weeks, in one centre the first stay lasts one week. In addition, two of the obesity centres offer two additional stays, while one offers no additional stay.

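### The three-stay completer analysis selects patients partly on their weight outcome and leaves its control set undefined, so it cannot support an effectiveness claim

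*Protocol article*

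**What the plan says.** All references are to the protocol article.

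- Data analysis of quantitative data: two analyses are planned. Analysis (a) takes everyone who accepted the intervention. Analysis (b) is to be run "with only those patients who completed the intervention (i.e., they had three stays at an obesity centre". No order of importance is given. Neither definition says which controls belong to the set.
- Same section: the 2 x 3 repeated-measures analysis covers "the dependent variables (i.e., body weight, physical activity, eating style & behaviour, health-related quality of life".
- mHealth obesity intervention: "one criterion for another stay is that patients have not gained weight compared to their last stay". CASPAR is an option for the time between stays.
- Quantitative data collection methods: at centres offering the mHealth intervention, questionnaires are also sent to patients who could have further stays "but do not attend them (e.g., due to weight gain, another stay was not approved by the insurance provider". Patients of the other centres are followed up at six and twelve months by questionnaire.
- Control group: "two of the obesity centres offer two additional stays, while one offers no additional stay". No weight criterion is stated for these stays.

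**The concern.** A completer set is ordinarily suspect because adherent patients differ from the rest. Here the problem is more direct: weight is written into the route by which a patient reaches the second and third stays. Patients who gain are less likely to be in (b), and weight change is then compared in those who remain.

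No single primary outcome is named, but body weight is listed first, and the Background describes obesity interventions as needing "to achieve weight loss as a primary goal". One of only two announced analyses could therefore report a weight benefit that comes from the selection rule and not from the platform.

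Three stays is also a poor measure of mHealth exposure. CASPAR is used between stays, and its supervision can be cancelled for inactivity under a separate rule. A patient with little CASPAR use can have three stays, and so can a patient who declined CASPAR at the same centre.

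**Working it through.** **1. The plan's own figure.** Inputs from Sampling and participants: eta-squared 0.01, alpha 0.05, power 0.80, two groups, three occasions, correlation 0.30. With f² = 0.01/0.99 and N = 225, lambda = 225 x 0.0101 x 3 / 0.70 = 9.74 on 2 and 446 degrees of freedom, and power is 0.802. The stated 225 reproduces, as does 225 / (1 - 0.5) = 450. The sample size is not in question. As a yardstick, with an assumed SD of 8 kg for weight change and 112 against 113 patients, the difference detectable at 12 months is (1.96 + 0.84) x 8 x sqrt(1/112 + 1/113) = 3.0 kg.

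**2. What the text alone gives.** Three stays means passing the criterion for another stay twice. No weight gain is one such criterion, so inclusion in (b) depends on weight change in each interval. The centre with no further stay cannot supply patients with three stays. Its patients are either kept unfiltered or lost altogether, so the rule cannot act equally on all controls. The direction of the selection follows from this; its size needs assumptions.

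**3. Size, model A: two six-month changes, no group difference.** Assumed: SD s = 5 kg per interval, common mean change m, uncorrelated changes, full enforcement. Keeping only changes at or below zero shifts each interval's mean by -s·φ(m/s)/Φ(-m/s). For m = -3: 5 x 0.333 / 0.726 = 2.3 kg per interval, or 4.6 kg over two.

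| Mean per interval | Kept | 12-month mean, all | 12-month mean, kept | Shift |
|---|---|---|---|---|
| -3 kg | 53% | -6.0 | -10.6 | -4.6 |
| -1 kg | 34% | -2.0 | -8.7 | -6.7 |
| 0 kg | 25% | 0.0 | -8.0 | -8.0 |
| +1 kg | 18% | +2.0 | -7.3 | -9.3 |

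With correlations of -0.2 to 0.3 between the changes, the shift ranges from -4.1 to -10.0 kg.

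**4. Effect on the group comparison under model A.** Start with 112 and 113 patients and no true difference; means -3, -1 and 0 kg; 3,000 runs each; Hotelling T² on the two changes as the group-by-time test.

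| Filter | Difference at 12 months | False positives |
|---|---|---|
| None | 0.0 kg | 4 to 5% |
| Intervention group only | -4.6 to -8.0 kg | 99 to 100% |
| Intervention group only, half of gainers removed | -1.6 to -1.7 kg | 24 to 29% |
| Both groups identically | 0.0 kg | about 5% |

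**5. Size, model B: change from baseline at 6 and 12 months.** Assumed: mean -2 or -5 kg at each time, SD 5 or 9 kg (no smaller at 12 than at 6 months), correlation 0.7 or 0.8, no true effect.

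- Both filters fully enforced: 12 to 52% of patients remain, and their 12-month mean is 2.9 to 9.6 kg lower than in all patients.
- First filter only: 1.0 to 4.8 kg lower. This is not analysis (b), which needs both.
- Half of gainers still attend at each stay: 0.9 to 3.5 kg lower.

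If the SD may shrink between 6 and 12 months, the lower ends for the first and third lines fall to 2.1 and 0.5 kg. These shifts equal a between-group bias only if no control is filtered.

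**The case against.** A reader might infer that (b) is bound to show a benefit for CASPAR. The document does not support that, for three reasons.

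First, it does not say that controls enter (b) unfiltered. The bracketed definition speaks of three stays at a centre, not three stays with CASPAR. Patients who decline CASPAR attend the same centres and appear to face the same criterion, and two of the three control centres also offer two further stays. If three stays were required of everyone under the same criterion, the between-group bias would largely vanish, as step 4 shows.

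Second, no weight gain is only one criterion and its enforcement is not described. Partial enforcement gives a bias often below the 3 kg yardstick.

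Third, analysis (a) is planned, is listed first and is not filtered by stays. Patients who miss stays, expressly including those who gained weight, are sent questionnaires and asked for their own weight, and missing data are to be imputed or handled by full-information maximum likelihood. Their weights are thus not simply lost.

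All three points stand, and they limit the size and certainty of the bias. They do not rescue (b). Equal filtering is neither stated nor possible at the centre without further stays, and even equal filtering overstates weight loss within each group. The limitations in the Discussion cover patient choice and centre differences, not selection on the outcome. An analysis plan not shown might rank the analyses, but the article itself fixes this definition of (b).

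**Conclusion.** The concern holds in a conditional form. Analysis (b) selects partly on weight, by the article's own rules, and its control set is undefined. It can show a weight benefit without any effect of CASPAR if controls are filtered less than the intervention group.

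Under the model B assumptions, the 12-month shift is roughly 3 to 9 kg with full enforcement and unfiltered controls, about 1 to 3 kg if half of the gainers still attend at each stay, and close to zero between groups under identical filtering. The means, SDs and correlations are assumed, not taken from the document. The first range is a worst case for the group comparison, not an estimate of the bias that will occur. Analysis (a) is not affected by the stay filter, but since the article ranks neither analysis, (b) stands as an equal result on effectiveness.

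**What to change.** - Make (a) the sole basis for effectiveness conclusions. Word it as all patients in their assigned group, whatever stays they attended, with all controls retained, using centre weights or, for non-attenders, self-reported weights.
- Replace the three-stay definition in (b) with an adherence definition based on the provider's CASPAR usage data, fixed before analysis. State which controls it is compared with, and label it exploratory.

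The cost is a rewording of two analysis sets and a modest extra analysis, since the usage data are already to be supplied. The drawback is that there is no simple completer result, and the adherence analysis remains non-randomised and open to confounding. Weighting for the probability of adherence could be added but is not needed to cure this defect. The clinical criterion for further stays is not in question.

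### The completer analysis selects patients partly on weight change, one of the outcomes it tests, and states no matching restriction for controls

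*Protocol article*

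**What the plan says.** The section on data analysis of quantitative data plans two analyses. Analysis (a) is done "with all patients who agreed to participate in the intervention". Analysis (b) is done "with only those patients who completed the intervention (i.e., they had three stays at an obesity centre". The model is a two-group by three-time-point repeated-measures MANOVA on "the dependent variables (i.e., body weight, physical activity, eating style & behaviour, health-related quality of life").

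The section on the mHealth obesity intervention states that "one criterion for another stay is that patients have not gained weight compared to their last stay". The section on quantitative data collection shows that this criterion has consequences: it provides for questionnaires to be sent to patients at app centres who could have further stays "but do not attend them (e.g., due to weight gain, another stay was not approved by the insurance provider"). For patients at app centres the two follow-up measurements are planned for the second and third stays. According to the body weight section, the centre supplies the weight if the patient agrees, and patients not at a centre report it themselves.

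Controls come from two sources. At app centres, "those who do not want to take part in such an intervention will be assigned to the control group". The others come from three centres without the app, of which "two of the obesity centres offer two additional stays, while one offers no additional stay". The control group section states no weight criterion for these centres.

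**The concern.** Analysis (b) defines its set by an event after baseline, having had three stays, and that event depends partly on weight change. Intervention patients who regained weight are therefore less likely to be in the set, whatever the app did. If the comparison group keeps its own regainers, the group-by-time contrast on weight contains a difference produced by the entry rule.

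This is separate from missing data and from app use. It would remain if every weight were observed and every patient used the app fully, so the planned imputation or full-information likelihood does not address it. The limitations in the Discussion cover self-selection into the app and differences between centres, but not this later selection. At stake is a completer benefit on weight being read as evidence of effectiveness, which is the study's primary purpose.

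**Working it through.** **1. The plan's own figure.** The sample size is not in question. It uses "Conservatively estimating the effect size by *η*^2^ = 0.01, *α* = 0.05, 1-*β* = 0.80, with two groups", a correlation of 0.30 and three occasions. With f² = 0.01/0.99 = 0.0101, the noncentrality is λ = f²·N·m/(1 − ρ) = 0.0101 × 225 × 3/0.70 = 9.74 on 2 and 446 degrees of freedom. Power is 0.802 at N = 225, and 225/(1 − 0.50) = 450. Both stated numbers reproduce.

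**2. Set-up of the check.** The document gives no mean, SD or correlation for weight change, so all inputs below are assumptions. Let d1 be the change from baseline to 6 months and d2 the change from 6 to 12 months, jointly normal, with no app effect. Strict enforcement keeps a patient only if d1 ≤ 0 and d2 ≤ 0. The spurious advantage is the mean change in patients kept minus the mean change in all patients, which is what a comparison with unfiltered controls would show.

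**3. Central case by hand.** Take means −4 and +1 kg, SDs 7 and 5 kg, correlation 0. For each interval, with a = −μ/σ, the pass probability is Φ(a) and E[d | d ≤ 0] = μ − σφ(a)/Φ(a).
- First interval: a = 4/7 = 0.571, Φ = 0.716, conditional mean −7.31 kg.
- Second interval: a = −0.2, Φ = 0.421, conditional mean −3.65 kg.
- Share passing both: 0.716 × 0.421 = 0.30.
- 12-month change: −10.96 kg in those kept against −3.0 kg in all, a spurious advantage of about 8.0 kg (3.3 kg at 6 months).

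**4. Imperfect enforcement.** If each gate stops only half of gainers, the excess per interval is 0.5σφ(a)/[1 − 0.5(1 − Φ)].
- First interval: 0.5 × 7 × 0.339/0.858 = 1.38 kg.
- Second interval: 0.5 × 5 × 0.391/0.710 = 1.38 kg.
- Total: about 2.8 kg, with 61% kept.

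If each gate stops a quarter of gainers, the total is about 1.2 kg.

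**5. Range under strict enforcement.** Simulated over first-interval means −2 to −6 kg (SD 5–8), second-interval means 0 to +2 kg (SD 4–6) and correlation −0.3 to +0.3:

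| Quantity | Range |
|---|---|
| Pass both gates | 14–47% |
| Spurious advantage, 12 months | about 3.3–12.5 kg |
| Spurious advantage, 6 months | about 0–6.3 kg |

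**6. A more favourable course.** With −4 kg in each interval, SD 4 and correlation 0, a = 1 and 71% pass both gates. The 12-month change is −10.3 kg against −8.0 kg, an advantage of 2.3 kg. At half enforcement it is 2 × 0.5 × 4 × 0.242/0.921 = 1.05 kg.

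**7. How much depends on the controls.** Welch test on 12-month change, 112 per group before filtering, strict enforcement, correlation 0, 2,000 runs, no app effect. Entries are the percentage of runs significantly favouring the app:

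| Mean per interval, SD | No control filtered | Two thirds of controls filtered | All controls filtered |
|---|---|---|---|
| 0 kg, 4 kg | 100% | 99% | 2.6% |
| −2 kg, 4 kg | 100% | 72% | 2.5% |
| −4 kg, 4 kg | 88% | 26% | 2.1% |
| −2 kg, 6 kg | 100% | 87% | 3.2% |

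With all controls filtered, the mean difference is about zero and the two-sided rejection rate about 5%.

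**The case against.** The strongest reply is that completion is defined by stays and not by app use, so controls could be held to the same rule. That is partly right. Digital supervision is an option within the stay programme, so decliners at app centres may face the same weight criterion, and two of the three control centres offer two further stays. A reader might infer that controls cannot be filtered alike at all; the documents do not support that. What they support is narrower. The analysis section states no such restriction, no weight criterion is given for the control centres, and one centre's patients could never have three stays. Equal restriction of all controls would mean dropping that centre's patients.

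A reader might also infer that completers' recorded weights can never rise from one measurement to the next. That goes too far. Absence of gain is one criterion among others, insurer approval is mentioned too, and the document does not say which weight from the first stay is the reference or when eligibility is assessed. Study weight need not equal the weight used for eligibility. The partial-enforcement results allow for this.

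Finally, a completer analysis beside a full-set analysis is common. Analysis (a) keeps everyone who agreed, with questionnaires sent to non-attenders, including those who gained weight. The order of precedence between (a) and (b) may be settled in an analysis plan not shown, so its absence here is not held against the protocol. These points limit the harm but do not make the weight comparison in (b) interpretable.

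**Conclusion.** The point stands in limited form. As written, (b) selects intervention patients partly on a variable that it then tests, and in the simulations unequal filtering favours the intervention on 12-month weight with no app effect. The kilogram figures rest on assumed weight courses, and the largest also on strict enforcement and wholly unfiltered controls; they illustrate the bias and do not estimate it for this trial. The bias shrinks as more controls pass the same gate and vanishes in simulation when all do.

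A reader might conclude that the whole effectiveness evaluation is compromised. It is not: the filter does not touch (a), and within (b) it acts directly only on body weight, one of several dependent variables. This is something the plan should fix, not a flaw that invalidates it.

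**What to change.** In the section on data analysis of quantitative data:

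- State that the conclusion on effectiveness for body weight rests on analysis (a), using the questionnaire follow-up of patients who do not attend further stays.
- Drop the between-group comparison of weight from (b), or report weight in (b) only descriptively, with a statement that patients with three stays were subject to a criterion of no weight gain.

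This takes two sentences and no new data, because follow-up of non-attenders is already planned. The price is losing a completer result on weight that would probably have looked more favourable. No change to the clinical criterion for further stays is proposed.
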